## Abstract

**Background:**

Health literacy is the degree to which individuals have the ability to find, understand, and use information and services to inform health-related decisions and actions for themselves and others, whether at home, at the workplace, in the community, marketplace, healthcare sector, or the political arena. The main aim of this project is to measure health literacy in the adult population living in the municipality of Leiria over the next 10 years. As secondary objectives it is intended to characterize anxiety and depression, metabolic risk and health behaviors in the same population and over the same period.

**Methods:**

This is a prospective cohort study that collects data on HL, anxiety and depression, health characteristics, health behavior and sociodemographic data. The study population will be composed by adults (≥ 18 years old) who are non-institutionalized and living in private households in Leiria. The random sample is stratified by gender and age groups. A face-to-face interview will be conducted with the Computer Assisted Personal Interview at baseline. Follow-up will be carried out every 2 years via telephone call. The association between independent variables and health literacy is examined by means of variance analysis with measurement repetition, and taking into consideration follow-up.

**Discussion:**

The LiSa project is a population-based study, derived from a random sampling technique that will allow the analysis of health outcomes in a representative sample of the population of the municipality of Leiria. The LiSa study will be a valuable resource for epidemiological research, as it will provide fundamental information to improve public health policies regarding health literacy in Portugal.

**Trial registration:**

Clinical trials: NCT05558631 (registered on 26/09/2022).

**Supplementary Information:**

The online version contains supplementary material available at 10.1186/s12889-024-19148-8.

## Background

According to the World Health Organization (WHO), health is considered “a state of complete physical, mental and social well-being and not merely the absence of disease or infirmity” [1]. Currently, health constitutes an essential axis of development that crosses and involves all sectors of activity, implying the dissemination of health as policies and the active participation of all citizens.

Health literacy (HL) is a topic that has been gaining increasing importance over the last few decades [2]. HL involves the knowledge, motivation and skills to access, understand, evaluate and apply health information in ways which promote and maintain good health [3]. Citizens with a higher level of HL find it easier to make everyday decisions related to healthcare, disease prevention, and health promotion to maintain or improve quality of life [4]. In recent decades in Portugal, the promotion of citizens’ HL has been identified as the way to improve health care, emerging as a concern in the definition of health policies. This is because different studies have shown that an inadequate level of HL can have significant implications for health outcomes, the use of health services and, consequently, health spending [5].

Studies indicate that the incidence of mental illness is increasing, with anxiety and depression being among the most common illnesses in the community [6, 7]. Patients with depression typically experience symptoms of anxiety, and those with symptoms of anxiety also experience depression. It can be difficult to discriminate between these two conditions, however both depression and anxiety disorders require specific and appropriate treatment, as they are associated with significant morbidity and mortality [7].

The gap between individuals who need mental health care and those who receive appropriate care is also a concern, as up to 70% of individuals who need mental health treatment fail to access the services they need [8]. Barriers to access treatments include lack of access to services, the potential client’s limited overall understanding of therapy treatment, and the perception that therapy treatment is too demanding or not relevant to the presenting concerns. These barriers are directly related to (lack of) HL [9].

Given these issues, it is necessary educate about the disease, focusing on the individual drivers which enables empowering citizens with knowledge to make conscious and informed decisions about the promotion of individual and collective health.

In 2021, the Municipality of Leiria prepared the Municipal Health Strategy, a document that serves as a tool to guide the development of health policies and intervention strategies of the Municipality. The document’s SWOT analysis presented HL and mental health as one of the weaknesses in the municipality, while hypertension and diabetes were identified as the leading health problems [10]. The Municipal Health Strategy is a strategic document, aligned with the main documents in the health area, namely the National Health Plan [11] where one of the main objectives are the reduction of alcohol consumption and exposure to tobacco.

Thus arises the LiSa study, a cohort study in Leiria, where citizens will be the essential source of information. The main aim of this project is to measure health literacy in the adult population living in the municipality of Leiria over the next 10 years. Concurrently, it is intended to characterize anxiety and depression and metabolic risk in the same population and over the same period.

## Methods

### Study design

The study is being developed and implemented by a multidisciplinary, multicenter team (researchers, health professionals, designers, mayors, among others). It is a prospective, longitudinal, closed cohort study over the next ten years with five data collection points. The guidelines from observational studies in epidemiology (STROBE) were applied to the study design [12]. The first data collection (baseline) will be carried out through an individual door-to-door interview, with a pre-established route, while the remaining data collection points will be managed via telephone.

To account the expected loss of participants to follow-up over time, we interviewed experts in cohort studies and potential study participants with the intention of helping and advising us in developing the study design. For that we used service design methodologies, namely informal interviews, and user groups definition.

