### Study population

The study population will be composed by adults (≥ 18 years old) who are non-institutionalized and living in private households in Leiria. Exclusion criteria will be: residents in hospitals, nursing homes, military barracks, or prisons, and residents unable to speak Portuguese or with a complete inability to respond to the questionnaire, either directly or through a person living with them [13].

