### Sample size

Residents of the municipality of Leiria aged 18 years or more. A sample size of 4003 (2001 males and 2002 females) were determined. A random sample stratified by gender and age groups (18–29, 30–64, 65 or more), for a confidence level of 95% and margin of 5% error was computed, in this case the sample need to collect should be 2287 participants. However, from previous studies [14] it is known that there is a high dropout rate in longitudinal studies, reaching approximately 50% in the 3rd wave. As if pretending to make 5 waves, the sample was increased by 75%. In other words, considering a dropout rate of 75%, data from 4003 participants should be collected. See Table 1.

**Table 1 Tab1:** Sample size of LiSa cohort study

	Leiria’s population		Sample size		+ 75% dropout	
	Male	Female	Male	Female	Male	Female
18–29 years	9367	9165	380	380	665	665
30–64 years	30,295	32,625	383	383	670	670
65 ou + years	9632	12,404	380	381	665	667
**Total**	**49,294**	**54,194**	**1143**	**1144**	**2001**	**2002**

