### Follow-up

The collection of new data will be carried out every 2 years via telephone call.

One of the approaches to mitigate the abandonment of participants (loss to follow-up) is to ensure good communication between the study team (interviewers, researchers, health professionals, designers, mayors) and cohort participants, using effective communication channels, updated, and provide quick feedback on health information to the participant.

The reasons why participants drop out of the study will be documented in order to analyze the bias of the study results.

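### In a closed cohort only the baseline wave represents Leiria's adult population; later waves describe ageing baseline residents and should not be reported as levels or trends for all adults

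*Protocol article*

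**What the plan says.** All places are in the protocol article.

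- **Design.** Study design: "It is a prospective, longitudinal, closed cohort study over the next ten years with five data collection points". Baseline is a door-to-door interview. Every later contact is by telephone, and under Follow-up "The collection of new data will be carried out every 2 years via telephone call". Recruitment is described at baseline only, and no refreshment sample or later entry is mentioned.
- **Aim.** Background: to "measure health literacy in the adult population living in the municipality of Leiria over the next 10 years". The Abstract gives the same aim, and the main Discussion repeats it with two-yearly measurement. The secondary objective in the Background is to "characterize anxiety and depression and metabolic risk in the same population and over the same period".
- **Eligibility.** Study population: "The study population will be composed by adults (≥ 18 years old) who are non-institutionalized and living in private households in Leiria".
- **Representativeness.** The Abstract's Discussion says that random sampling will allow the study of "health outcomes in a representative sample of the population of the municipality of Leiria". It names no wave.
- **Sample size.** "A random sample stratified by gender and age groups", with a 5% margin at 95% confidence, then enlarged by 75% in every stratum to allow for dropout over five waves. The text does not say whether the strata refer to age at baseline or to current age at each wave.
- **Analysis.** Statistical analysis: change in health literacy is assessed by repeated-measures analysis of variance, with sociodemographic characteristics added by linear regression.

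**The concern.** The aim reads most naturally as a statement about whoever is an adult in Leiria at each point of the ten years. A closed cohort meets that only once. After baseline everyone in it ages together, no new young adults enter, and people who settle in the municipality later are absent. Full retention would not change this.

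What is at stake is the conclusion drawn from later waves. Between two waves each participant becomes two years older, so the average change contains an ageing effect as well as any real shift in health literacy in the municipality. Adding sociodemographic covariates does not by itself separate the two. The article directs its results to public health policy and national decision-makers. Under the aim as worded, such readers could take a cohort change for a population trend, or a later-wave level for the current level among all adults.

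**Working it through.** **Inputs.** Entry at age 18 or over (Study population); two-year interval (Follow-up); five points and ten years (Study design); stratum populations and sample sizes (Table 1).

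**The plan's own figures.** Each stratum requirement is multiplied by 1.75: 380 × 1.75 = 665. Overall, 2287 × 1.75 = 4002.25, against 4003 stated. The requirements of 380 to 383 per stratum are close to the usual formula for a proportion. Taking p = 0.5 (an assumption), 1.96² × 0.25 / 0.05² = 384.15, and a finite population correction gives 369 to 380. So the 5% margin was set within each gender-by-age stratum.

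**Timing.** Five points two years apart, starting at baseline, fall at years 0, 2, 4, 6 and 8, whereas the text speaks of ten years. That mismatch is a separate matter, so both end points are shown.

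**Minimum age** = 18 + years since baseline.

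**Size of the youngest band.** Adults: 49,294 + 54,194 = 103,488. Aged 18–29: 9,367 + 9,165 = 18,532, or 17.9%. Recruited at 18–29: 665 + 665 = 1,330.

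**Assumptions.** Ages are evenly spread over the 12 single years from 18 to 29, and the population is stable. At year *y*, the uncovered share of the band is *y*/12, the uncovered share of adults is (*y*/12) × 17.9%, and the number recruited at 18–29 who are still under 30, with no dropout, is 1,330 × (1 − *y*/12).

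| Year | Minimum age | Uncovered share of adults | Still under 30, no dropout |
|---|---|---|---|
| 0 | 18 | 0% | 1,330 |
| 2 | 20 | 3.0% | 1,108 |
| 4 | 22 | 6.0% | 887 |
| 6 | 24 | 9.0% | 665 |
| 8 | 26 | 11.9% | 443 |
| 10 | 28 | 14.9% | 222 |

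In people, 8/12 × 18,532 ≈ 12,355 at year 8, and 10/12 × 18,532 ≈ 15,443 at year 10.

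**Sensitivity.** The documents do not split the band by single year. If the uncovered part were anywhere from 50% to 90% of the band, the gap would be 0.5 × 17.9% ≈ 9% to 0.9 × 17.9% ≈ 16% of adults. It cannot exceed 17.9% on age alone. People who move in after baseline add to it, but the documents give no figure for them.

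**Consequence for the strata.** Table 1 sets 380 + 380 = 760 for ages 18–29. If the strata meant current age at each wave, about 443 would be available at year 8 with perfect retention. Reaching 760 would need 760/1,330 = 57% of those recruited at 18–29 to be aged 18–21 at entry. If the strata mean age at baseline, ageing does not empty them. The article should say which is meant.

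**The case against.** The strongest reply is that the aim can be read as following the adults who live in Leiria at baseline. The Background refers to one and the same population over the period, the design is openly a closed longitudinal cohort, and eligibility is defined at entry. The only follow-up analysis described is change in health literacy. The main Discussion justifies the longitudinal design by life-course detail and the ordering of events, not by population surveillance. No wave-by-wave population estimate is announced. All of this stands, and it means the planned longitudinal analysis suits the design. It does not remove the need to say which population the aim concerns, because the article never does.

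Four stronger readings might be inferred, and the documents do not support them:

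- **That the study cannot measure health literacy in Leiria's adults.** Baseline covers all eligible adults, and on the figures above the ages still covered at the last wave are about 85% to 88% of adults, before newcomers.
- **That about 111 young adults would remain at year 8 against 760 required.** The figure 443 × 0.25 ≈ 111 mixes in the 75% dropout. With no ageing at all, 1,330 × 0.25 ≈ 333 is already far below 760. That shortfall belongs to the dropout allowance, which is a different issue.
- **That the Abstract's Discussion states a ten-year aim.** It does not. Its representativeness wording is defensible for the sample as drawn and only needs tying to that sample.
- **That FINDRISC must be reported without age.** Age is one of the score's eight parameters, and a rise as participants age reflects what the score is built to measure. A version without age is optional.

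**Conclusion.** The point holds as a limit on what later waves represent. Only baseline speaks for Leiria's adult population. Later waves speak for people who were adult residents at baseline, with nobody under 26 at year 8 (or under 28 at year 10) and nobody who arrived after baseline.

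The minimum ages follow directly from the design. The shares of 11.9% and 14.9% of adults, and the 443 of 1,330 still under 30 at year 8, rest on an even age spread within 18–29; the shares also assume a stable population. Wave-to-wave change is sound as within-person change and is not a population trend. No planned estimate is shown to be invalid, so this is something that should be fixed and not a fatal flaw.

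**What to change.** 1. In the Abstract, the Background and the main Discussion, restate the aim: baseline estimates health literacy in Leiria's adult population, and later waves estimate change among people who were adult residents at baseline.
2. In the Abstract's Discussion, tie the representativeness wording to the baseline sample.
3. Under Sample size, state that the Table 1 strata are defined by age at baseline, and that the 5% margin for the current adult population applies to baseline only.
4. If a population level is reported at a later wave, restrict it to the ages still covered (26 and over at year 8, 28 and over at year 10) and standardise it by current age to Leiria's population. Compare it with the baseline sample limited to the same ages and standardised to the same distribution, and say that it omits people who moved in after baseline.

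The cost is wording and a few lines of analysis text, with no new participants or data. The downside is a narrower claim than a ten-year picture of all adults.

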### Study population

The study population will be composed by adults (≥ 18 years old) who are non-institutionalized and living in private households in Leiria. Exclusion criteria will be: residents in hospitals, nursing homes, military barracks, or prisons, and residents unable to speak Portuguese or with a complete inability to respond to the questionnaire, either directly or through a person living with them [13].

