### Data collection

At baseline a face-to-face interview will be conducted with the Computer Assisted Personal Interview (CAPI) system: all interviewers have a tablet with the software which will provide the questionnaire. The questionnaire was designed by LiSa’s research team. Both the survey and software performance were tested in a small sample of subjects, and results validated by the LiSa research team before being used by the interviewers. It is estimated it will take approximately 30 min to complete the survey.

Since there is no reliable list of households in Portugal, a random selection of points in the map of each location will be performed. Addresses will be selected, and afterwards the “random walks” will start. Interviewers will register each selected address and, if someone is at home, they will collect information on age and gender of the different people living in that address, and will give information about the study. After validation of the selected address and inhabitants, the interviews will be scheduled, or if the person is available will be immediately asked to answer the questionnaire. In order to assure the successful data collection, up to three visits to each address (one during the weekend) will be made [13]. At each address, the person whose birthday is closest to the day of the visit (aged 18 years or older) will be selected for the interview.

Between February and April 2023, five interviewers conducted a pilot study, in the largest parish in the council, with the aim of testing the proposed methodology. Taking into account that data collection went well, we will maintain this data collection methodology and start the first data collection in February 2024.

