### Health literacy

HL will be measured through European Health Literacy Survey Questionnaire short-form version (HLS_19_-Q12). To measure HL in an adequate way for public health-oriented surveys of general population in Europe, the Health Literacy Survey (HLS-EU) was conducted in 2012 [16] using a new measurement tool developed from the conceptual model of Sørensen et al. [17]: the “47-item European Health Literacy Survey Questionnaire” (HLS-EU-Q47) [18]. HLS-EU was developed to measure HL in populations [18] based on a conceptual framework reflecting four information-processing dimensions (i.e., accessing, understanding, appraising, and applying) within three health domains (i.e., health care, disease prevention, and health promotion) [17]. Each item in the questionnaire assesses the perceived difficulty of a specific health-related task for the respondent. Since 47 items were excessively time-consuming for some HL researchers’ short forms have been validated in several languages to be used in the European Health Literacy Survey [4, 19, 20] The HLS_19_-Q12 was translated and validated in a previous study in Portuguese population [3]. The scale contains 12 items that measure HL. Each item assesses the perceived difficulty of completing a specific health-related task by asking “On a scale from very difficult to very easy, how easy would you say it is to [e.g, find information on symptoms of illnesses that concern you]?” Each item is rated on a 4-point Likert-type scale (1, very difficult; 2, fairly difficult; 3, fairly easy; 4, very easy). To correctly assess respondents’ health literacy, participants must answer at least 10 of the 12 questions. The general HL index (G-HL12) is calculated as follows: G-HL12 index = (mean − 1) x (50/3). Four levels of HL are defined: inadequate (0–25), problematic (25.1–33), adequate (33.1–42), and excellent (42.1–50) [21].

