### Anxiety and depression

To evaluate symptoms of anxiety and depression we applied the Hospital Anxiety and Depression Scale (HADS) Portuguese validated version [22]. The HADS was originally developed by Zigmond and Snaith [23] as a screening tool to apprehend clinically significant states of anxiety and depression in a non-psychiatric hospital setting. Individual anxiety and depression scores were calculated by summation of the appropriate seven items and thus can range from 0 to 21, with higher scores indicating higher levels of anxiety or depression, respectively. In both subscales, a score between 0 and 7 is “normal,” between 8 and 10 “mild,” between 11 and 14 “moderate,” and between 15 and 21 “severe” (idem). Presence of anxiety and depression symptoms was defined when HADS scale was ≥ 11, since Snaith suggested a score ≥ 11 was indicative of “caseness” to a mood disorder [24]. This scale is used in a lot of observational studies [14, 25].

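### The eligibility rule lets a household member respond for a participant without limiting this by item, although health literacy and HADS are self-perception and symptom scales

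*Protocol article*

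**What the plan says.** The Study population section of the protocol article lists, among the exclusions, residents "with a complete inability to respond to the questionnaire, either directly or through a person living with them". Someone who cannot respond directly but can respond through a cohabitant is therefore not excluded. The criterion refers to the questionnaire as a whole.

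The Background section makes health literacy (HL) the main aim. The Health literacy section describes the parent instrument in these terms: "Each item in the questionnaire assesses the perceived difficulty of a specific health-related task for the respondent". It describes the 12-item form in the same way: "Each item assesses the perceived difficulty of completing a specific health-related task". For a score to be valid, "participants must answer at least 10 of the 12 questions".

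The Anxiety and depression section says: "To evaluate symptoms of anxiety and depression we applied the Hospital Anxiety and Depression Scale (HADS) Portuguese validated version". Neither instrument section says who may answer.

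The Data collection section describes one electronic questionnaire ("all interviewers have a tablet with the software which will provide the questionnaire") and no separate form for assisted interviews. The Study validity section breaks its quality checks down by interviewer team, place, age and sex, but not by who answered. The Statistical analysis section studies change in HL by repeated-measures analysis of variance and does not mention respondent type. Baseline is a home interview and later waves are by telephone.

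**The concern.** An eligibility rule of this kind does little harm for facts such as schooling, a diagnosis or body weight, which a cohabitant may know. HLS19-Q12 and HADS ask for something else: how hard the person finds a task, and how the person feels. If a cohabitant gives their own judgement, the score describes the cohabitant's view or guess.

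Two things are at stake. First, the baseline HL and HADS levels could contain answers that are not the participant's, most likely in the older strata, where assistance is plausibly most common. Second, the cohort is closed and followed for ten years. A participant who answers in person at baseline and through a cohabitant at a later telephone wave would show an apparent change in HL that comes from the change of respondent. Unless the data record who answered, the analysis cannot separate the two.

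**Working it through.** **Reading the sections together.** There are three possible meanings of responding through a cohabitant.

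1. *Relay.* The cohabitant passes on the participant's own answers, for example where hearing or speech is impaired. The score is then the participant's, the 10-of-12 rule can be met, and nothing conflicts.
2. *Substitution on all items.* The cohabitant answers HLS19-Q12 and HADS in the participant's place. This conflicts with the Health literacy section's definition of the items.
3. *Substitution on factual items only.* A participant who cannot answer the HL items is eligible but cannot meet the 10-of-12 rule. That person fills a place in Table 1 without a primary outcome.

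The eligibility wording allows all three. Only the first leaves the HL results unaffected.

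**Size.** The document gives no proxy share and no proxy effect, so every effect size below is an assumption.

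*Planned number aged 65 or over (Table 1, after the 75% increase).* Men: 380 × 1.75 = 665. Women: 381 × 1.75 = 666.75, rounded up to 667. Total 665 + 667 = 1,332, as in the table.

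*What a difference on the index means.* The index is (mean − 1) × 50/3. A difference of 5 points is 5 ÷ (50/3) = 0.30 in the item mean, or 0.30 × 12 = 3.6 items rated one category differently. By the same formula, 3 points is about 2.2 items and 10 points is 7.2 items.

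*Shift in a mean* = share substituted × difference between substitute and self-report.

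| Assumed share | People among 1,332 | Shift at 3 points | Shift at 5 points | Shift at 10 points |
|---|---|---|---|---|
| 3% | 40 | 0.09 | 0.15 | 0.30 |
| 10% | 133 | 0.30 | 0.50 | 1.00 |

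The shift could go in either direction.

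*Population mean.* Table 1 gives 9,632 + 12,404 = 22,036 residents aged 65 or over, out of 49,294 + 54,194 = 103,488, which is 21.3%. If substitution occurs only in that age group, the 5-point case shifts the population-weighted mean by 0.213 × 0.15 = 0.03 to 0.213 × 0.50 = 0.11 points.

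*One person.* The problematic band runs from 25.1 to 33, a width of 7.9 points. A 5-point respondent effect is 5 ÷ 7.9 = 63% of that width, so a change of respondent could move a person from one HL level to another.

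*Change between waves.* If a share s of those seen at two waves switches from self to substitute, the spurious mean change is s × difference, so the same table applies with s as the share.

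**The case against.** A reader might infer that cohabitants do answer the HL and HADS items, and that the primary outcome is therefore measured on the wrong person for some participants. The document does not support that. The sentence is an exclusion criterion, not a response rule for any instrument, and no section says that a cohabitant answers those items. The relay reading is natural: it is the resident who responds, and the Health literacy section speaks of participants answering. The interviewer's manual, the electronic form and the source cited for the criterion are not shown, and any of them may settle the matter.

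The likely bias in means is also small. With an assumed standard deviation of 8.3 points, the 95% half-width for the mean of 1,332 people is 1.96 × 8.3 ÷ √1,332 ≈ 0.45 points under simple random sampling. Most of the 0.15–0.5 range lies within that.

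Finally, dropping every assisted interview would exchange possible measurement error for non-random missing data among older or ill participants.

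Much of this stands. It removes any claim that the outcome is known to be mismeasured, it limits the expected size, and it argues against discarding assisted interviews wholesale. It does not remove the ambiguity. The criterion is stated in the article itself, carries no item restriction, and as written permits substitution on scales for which substitution is not valid. Sampling error is no defence against a respondent switch either, because that would appear as individual change.

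**Conclusion.** The point holds as a defect of specification. The eligibility rule admits people who respond only through a cohabitant and does not confine this to items that a cohabitant can answer, while the primary outcome and HADS depend on the participant's own perception and symptoms. If cohabitants substitute, those scores are invalid for the people concerned, and a switch between waves imitates a change in HL. If they only relay, there is no bias, but the text should say so.

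The document does not show how often either happens. Under the assumptions above (3–10% of those aged 65 or over, 5 points), the effect is 0.15–0.5 points in that age group's mean and 0.03–0.11 in the population mean. It is probably small overall and matters more for individual trajectories and HL levels. The share, the effect and its direction are all assumed. This is a cheap improvement worth making, not a flaw that undermines the study.

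**What to change.** - In the Study population section, state that a cohabitant may relay the participant's own answers and may answer factual items, but may not substitute for the participant on HLS19-Q12 and HADS.
- Add a field to the home and telephone questionnaires, at every wave, for who answered these scales: self, relayed or substituted. If baseline interviews have already been done, the confirmatory telephone contacts described under Study validity could be used to establish this afterwards.
- Base the primary HL and HADS analyses on self-given or relayed answers. Add a sensitivity analysis that includes any substituted answers already collected.
- Report how many participants lack a valid HL score for this reason, by stratum and wave.

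The cost is one data field, a sentence in the eligibility text and a short addition to interviewer training. The downside is a small loss of HL and HADS data, mainly in the strata aged 65 or over. The results would then refer to adults able to give their own answers, and reports should say so.
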